
### Statistical analyses

3.10

To test the hypotheses of the study various inferential statistical tests will be performed with a comparison of means and medians (Student *t* test and Wilcoxon) using the SPSS statistical package for Windows. In the inferences, a significant result will be considered if the probability of type I error is ≤0.05 (5%).

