### Study design

3.1

This is a randomized, crossover, triple-blind, sham-controlled study. The study was registered on December 28th, 2017 with Brazilian Registry of Clinical Trials (ReBec) as “The Effects of Transcranial Direct Current Stimulation on Attention and Inhibitory Control of Children and Adolescents with Attention-Deficit/Hyperactivity Disorder (ADHD): a randomized, sham-controlled, triple blind, cross-over trial” (http://www.ensaiosclinicos.gov.br/rg/RBR-7h5qzf/).

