### Sample calculation

3.4

The sample size calculation was performed based on a pilot study. We used the variable “errors by default” of visual attention test (TAVIS) test as the primary outcome. Considering the level of significance of 5%, the power of 80%, the mean difference between paired groups of 1.2 and the standard deviation of 1.24, the sample size calculation resulted in 11 subjects. Assuming 25% of dropout, our final sample size was 14 subjects.

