### Interventions

3.8

After selecting the sample according to the aforementioned criteria and neuropediatric evaluation, children diagnosed with ADHD will participate in a neuropsychological assessment in which the intellectual level estimation and its performance in the processes of attention, operational memory, and inhibitory control will be investigated. The Swanson, Nolan, and Pelham – IV questionnaire assessing the diagnostic criteria for ADHD from the DSM-5 will be applied to the parents.

A total of 15 individuals will be selected, randomly assigned in 2 groups, 8 of whom were initially in the tDCS group and 7 in the sham group. It will be made clear to those responsible and to the relevant child that tDCS may not be applied. During the stimulation, the same conditions will be reproduced in both groups, except for active treatment in the sham group. The patient will be informed about the procedure before the beginning of the study, with the device being used for a first perception of the current flow for a few seconds.

The tDCS consists of an application of a direct electric current of low amplitude (2 mA) for 30 minutes from 2 electrodes (5 cm × 7 cm) embedded in saline solution. The anode will be positioned in the left anterior dorsal prefrontal cortex (F3 according to the electroencephalogram system 10–20) and the cathode in the supraorbital region on the opposite side. The device used will be the Striat (Ibramed, Amparo-SP, Brazil), approved by the Brazilian National Health Agency (ANVISA). During the stimulation period participants will participate in playful activities involving memory and attention, such as the “Super Lynx” and “Genius” games. They will be carried out by an appropriately trained individual, in 5 sessions, 1 per day, and in the presence of a physician trained to deal with possible intercurrences. Participants may withdraw from participating in the study at any time according to the informed consent form.

After 1 month, the groups will be crossed. Thus the 8 children initially stimulated will be part of the sham group in the second phase and the children initially in the sham group will then receive active stimulation. Before and after the new cycle of stimulation, neuropsychological evaluations will be carried out by applying the aforementioned tests. The family, the research subject, the evaluators, and the statistician will be blind to the subject's group.

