#### Neuropsychological evaluation

3.9.1

All participants will be evaluated by neuropsychological tests at 4 different moments: before the first cycle, with an intellectual screening and additional behavioral analysis; after the first cycle and before and after the second cycle. The tests will be applied by neuropsychologists with experience in the evaluation process and using the following instruments:

Characteristics of the sample:

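### Plain Student t and Wilcoxon tests leave the period effect of a two-period crossover in the error term, which can cost power; bias is small unless dropout is clearly uneven between sequences

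*Protocol article*

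**What the plan says.** Study design (3.1): "This is a randomized, crossover, triple-blind, sham-controlled study". Under Interventions (3.8), 15 children are split into two sequences, "8 of whom were initially in the tDCS group and 7 in the sham group", and cross over after one month.

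Neuropsychological evaluation (3.9.1): "All participants will be evaluated by neuropsychological tests at 4 different moments", that is, before and after each of the two cycles. The outcome tests are TAVIS-4, digit span, Corsi blocks and the NEPSY-II inhibition subtest.

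Statistical analyses (3.10) names the tests but not the contrast: "various inferential statistical tests will be performed with a comparison of means and medians", by Student t and Wilcoxon in SPSS at the 5% level. It does not mention period or sequence, or say which of the four assessments are compared.

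The intended contrast shows best in Sample calculation (3.4), which uses "the mean difference between paired groups of 1.2 and the standard deviation of 1.24" for a TAVIS error count and reports that "the sample size calculation resulted in 11 subjects". It then allows for 25% dropout.

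**The concern.** Attention, working-memory and inhibition tasks tend to improve with repetition, and each child meets the same battery four times within weeks. A difference between the first and second period that has nothing to do with tDCS is therefore plausible.

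In a two-period crossover such a difference pushes active minus sham one way in children who start on active and the other way in children who start on sham. A one-sample test on the pooled differences, which is what a paired t or signed-rank test is, treats this systematic split as random noise. The standard error grows and power falls. If the two sequences differ in size, the period effect also fails to cancel in the mean. With 15 children enrolled and about 11 expected to complete, there is little power to spare.

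**Working it through.** **Inputs.** Effect τ = 1.2 and SD of the paired difference s = 1.24 (3.4). Alpha 5%, taken as two-sided because that reproduces the plan's n. Sequence sizes n1 = 8 active-first and n2 = 7 sham-first (3.8). Completers: 15 × 0.75 = 11.25, so 11, taken as 6:5. The period effect π (period 2 better than period 1, in errors) is **not in the documents**. The values 0.3, 0.6 and 1.2 are assumptions, roughly a quarter, a half and one SD of the difference.

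**Step 1: reproduce the plan's figure.** Exact paired-t power uses a noncentral t with n − 1 df and noncentrality τ√n/s.
- n = 10: 1.2 × √10 / 1.24 = 3.06, power 77.7%.
- n = 11: 1.2 × √11 / 1.24 = 3.21, power 82.4%.

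So n = 11, as stated. The sizing is that of a plain paired t test.

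**Step 2: what a period effect does.** Active-minus-sham benefit centres on τ − π in active-first children and τ + π in sham-first children. With N = n1 + n2:
- bias of the plain mean = π(n2 − n1)/N
- expected SD of the pooled differences = √[s² + 4π²·n1·n2 / (N(N − 1))]

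Example at 8:7, π = 0.6: √[1.5376 + 4 × 0.36 × 56/210] = √1.9216 = 1.386.

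**Step 3: period-adjusted comparator.** The estimate is the average of the two sequence means, with SE = ½·s·√(1/n1 + 1/n2) and N − 2 df.
- 8:7: SE 0.321, noncentrality 3.74, 13 df, power 93.2%.
- 6:5: SE 0.375, noncentrality 3.20, 9 df, power 81.1%.

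These do not depend on π.

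**Step 4: power of the plain paired t** (exact at π = 0, otherwise 200,000 simulated trials per cell).

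| Split | π | Pooled SD | Bias | Plain power | Adjusted power |
|---|---|---|---|---|---|
| 8:7 | 0 | 1.24 | 0 | 93.6% | 93.2% |
| 8:7 | 0.3 | 1.28 | −0.02 | 92% | 93.2% |
| 8:7 | 0.6 | 1.39 | −0.04 | 88% | 93.2% |
| 8:7 | 1.2 | 1.75 | −0.08 | 67% | 93.2% |
| 6:5 | 0 | 1.24 | 0 | 82.4% | 81.1% |
| 6:5 | 0.3 | 1.28 | −0.03 | 79% | 81.1% |
| 6:5 | 0.6 | 1.39 | −0.05 | 71% | 81.1% |
| 6:5 | 1.2 | 1.76 | −0.11 | 44% | 81.1% |

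**Step 5: uneven dropout.** At 8:4 and π = 1.2, bias = 1.2 × (4 − 8)/12 = −0.4, so the plain estimate falls from 1.2 to 0.8 and its power to 26%; the adjusted test is unbiased with 81%. If three of 15 children drop out at random, all three come from the sham-first sequence with probability C(7,3)/C(15,3) = 35/455 = 7.7%.

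**Step 6: type I error of the plain test.** At 8:7 it is below nominal: 4.5, 3.2 and 0.9% for π = 0.3, 0.6 and 1.2. It rises above nominal when the split is extreme: at 8:3, about 6, 7 and 10%. With four random dropouts, 8:3 has probability C(7,4)/C(15,4) = 35/1365 = 2.6%.

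**The case against.** **The paired contrast is inferred.** Section 3.10 names two families of tests and no contrast. A two-sample Student t on period differences would be a correct crossover analysis and would also fit the words. This stands as a caution. Still, the sample calculation speaks of paired groups and its n reproduces as a paired t, so the plain paired test is the natural reading. The point rests on the tests that the article names, not on detail that a fuller plan might hold.

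**Each cycle has its own baseline.** If change within each cycle is analysed, practice carried into the second cycle is subtracted, and only a practice gain that differs between cycles remains. This stands too. The article does not say that changes are analysed, so the benefit cannot be assumed.

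**The period effect is a guess, and 1.2 is as large as the whole treatment effect.** This is correct. At 0.6 all 15 children still give about 88%, above the planned 80%. The shortfall against 80% needs either a very large period effect or the expected loss to about 11 completers.

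**Stronger readings that a reader might infer.** One is that the planned analysis is seriously biased. At 8:7 the bias is one fifteenth of π, at most 0.08 errors over the assumed range. Another is that false positives are inflated; at 8:7 the plain test is conservative. A third is that a null result would be uninterpretable. The estimate at 8:7 is nearly unbiased, only its interval is too wide, and the adjusted analysis can be run on the same data. The documents support none of the three.

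**Conclusion.** The concern holds as one of avoidable power loss of unknown size. The article sizes the trial on a paired difference, names only plain tests, and does not account for period although practice effects are plausible. On the plan's effect and SD, the loss against the adjusted test with 15 children is about 1, 6 and 26 points for assumed period effects of 0.3, 0.6 and 1.2 errors. With 11 completers it is about 2, 10 and 37 points, and even the smallest of these effects takes the plain test just below 80%.

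Bias is a secondary issue that matters only if completers are clearly uneven between sequences, for example 8:4.

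The figures assume that 1.24 is the SD of active minus sham free of any period effect. The article takes it from a pilot study whose design the sample calculation does not describe. They also assume normal differences and a period effect on whichever outcome is analysed, whether post-cycle score or change.

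**What to change.** In 3.10, replace the plain paired tests for the treatment contrast with a 2x2 crossover analysis, fixed before unblinding. Either of these will do:
- a linear mixed model with fixed treatment, period and sequence and a random child effect; or
- equivalently for children who complete both periods, a two-sample t test between sequences on within-child period differences, with the rank-sum test as the nonparametric version.

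State whether it is applied to each period's post-cycle score or to its change from the pre-cycle assessment.

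**Cost.** This is a change of wording, and SPSS can run both analyses. It uses one degree of freedom. If there is no period effect, the loss of power is 93.6 − 93.2 = about 0.4 points at 8:7 and 82.4 − 81.1 = about 1 point at 6:5. It is larger if completers are very uneven: 86.2 − 81.2 = about 5 points at 8:4 and 82.4 − 72.1 = about 10 points at 8:3. Those are also the splits where the plain test is most exposed to bias.

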### Ethics

3.11

The current project was submitted and approved by the Research Ethics Committee of the Medical School of Bahia, Federal University of Bahia in accordance with consent n° 2.351.121 of October 26th, 2017, on the understanding that:

(1)The research project does not include invasive procedures that expose participants to situations of risk;(2)Only children and adolescents who sign the consent form for minors and whose parents authorize their participation by duly signing the free and informed consent form will be included;(3)The researchers undertake to keep the child's identification confidential and use the data strictly for academic purposes, namely scientific discussions and the publication of scientific articles;

At the end of the data collection families will be informed about the results obtained in the neuropsychological tests and they will also be informed of the study's final results. Refusal to participate in the study or interruption of participation during the same will not affect any ongoing relationship with the child in respect of the University healthcare services.

## Discussion

4

The use of tDCS has already been described in the literature as a method of ADHD treatment with some controversial results. In a 2015 study conducted by Soltaninejad et al,^[10]^ 20 adolescents were stimulated with the objective of improving inhibitory control. They were tested during the stimulation process to compare the results between cathodic, anodic, and placebo stimulation. Studies show that the dorsolateral prefrontal cortex is involved with inhibitory control.^[7]^ Given that the left hemisphere is dominant for language in 95% to 99% of right-handed people and 60% to 70% of left-handers,^[50]^ and in order to stimulate the dominant hemisphere of participants, only right-handed individuals were included in the Soltaninejad study, in which the electrodes were positioned in the left dorsolateral prefrontal cortex and right supraorbital region. The intensity of current used in this study was 1.5 mA and the stimulation time was 15 minutes per session, with a 72-hour interval between 3 different sessions. According to the study there were no statistically significant differences between the results of the inhibitory control tests applied in anodic, cathodic, and placebo stimulation.^[10]^

In a 2016 study carried out by Bandeira et al,^[38]^ with 9 children and adolescents, electrodes of the same size and position were used, operating at a current of 2 mA, along with 30 minutes of stimulation for 5 sessions on consecutive days. Neuropsychological tests performed before and after the stimulation showed improvement of some functions such as selective attention and inhibitory control. However, the study was non-randomized and involved a reduced sample, making it necessary to develop a study with a more robust methodology and to enable a more accurate evaluation of the effects of tDCS on attention and inhibitory control and other neurophysiological parameters in a blind, randomized, sham-controlled setting.

In 2016, Breitling et al^[39]^ performed a cross-over study involving 21 patients with ADHD and 21 without the disorder in a control group, with cathodic and anodic stimulation and placebo performed on all patients with at least 1-week interval between them, with 35cm^2^ electrodes and a 1 mA current being used for 20 minutes. An analysis of the results of the neuropsychological tests carried out revealed that there was no significant effect of tDCS between the groups.

Following randomized, double-blind, sham-controlled studies were performed with adolescent dorsolateral prefrontal cortex stimulation, one of which showed improvement of executive function with anodic stimulation and improvement of inhibitory control with cathodic stimulation.^[51]^ Other study showed that anodic stimulation caused a significant reduction of the clinical symptoms of inattention and impulsivity in patients with ADHD compared to the sham-group.^[36]^ Moreover, in a different study anodal stimulation improved motor performance, but worsened accuracy in the working memory paradigm.^[42]^

We hope, with our randomized, cross-over, triple-blind, sham-controlled protocol, to find statistically significant results regarding patterns of attention and inhibitory control identified by the neuropsychological test battery performed.
